## Abstract

**Background:**

Suicide constitutes a cause of death which could be prevented by e-health programs accessible to the general population. Effective promotion has the potential to maximize the uptake of such programs. However, few e-health programs have been combined with promotion campaigns. The primary objective of this trial is to assess the effectiveness of a tailored promotion, at a local level, of a mobile application and website offering evidence-based content for suicide prevention (the StopBlues program), and to compare the effectiveness of two types of local promotion in terms of their impact on suicidal acts. Secondary objectives focus on the effectiveness of the promotion in terms of the intensity of utilization of the StopBlues program, help-seeking behaviors and the level of psychological impairment of program users.

**Methods/design:**

This is a three-arm, parallel-group, cluster-randomized controlled trial, with before-and-after observation. Thirty-four clusters, corresponding to geographical areas sharing a common local authority in France, will be included. They will be randomly assigned to one of the following arms with a ratio of 1:1:1: a control group; a basic promotion group in which promotion of the StopBlues program will be done by local authorities; and an intensified promotion group in which basic promotion will be supplemented by an additional one in a general practitioner’s waiting room. The primary outcome measure will be the number of suicidal acts within each cluster over a 12-month period following the launch of the intervention. Baseline data will be collected for each cluster over the 12-month period prior to the trial. Secondary outcomes will include length of use of the StopBlues program, measures of help-seeking behaviors and level of psychological distress among users of the program, as well as the cost-effectiveness and budgetary impact of its promotion. A more sustained promotion by local authorities will also be implemented after 12 months in the control group and assessed using the same outcome measures.

**Discussion:**

This research should contribute to the sparse evidence base regarding the promotion of e-health programs and will support the wider delivery of the intervention evaluated if proven effective.

**Trial registration:**

ClinicalTrials.gov, ID: NCT03565562. Registered on 11 June 2018

## Background

Suicide is a human tragedy, resulting from significant psychological distress, and is among the leading causes of death worldwide [1]. France is one of the most affected Western European countries, with around 11,400 deaths by suicide (13.8 per 100,000 inhabitants) and nearly 200,000 suicide attempts annually [2–4]. Moreover, surveys in the general population have estimated that one out of 20 French people has attempted suicide at least once over their life course [5]. The societal costs of suicide are also particularly high. In countries where it has been documented, the magnitude of the economic burden of suicide has been found to range from several million to several billion dollars per year depending on the size of the population [6–9].

Yet, suicide represents a cause of avoidable death which could be significantly reduced by effective prevention programs in the general population targeting the main challenges in the field of suicide prevention. These challenges include impaired upstream identification and care for people at risk, whereas early detection and management of mental disorders and suicide ideation has been identified as one of the current key priorities for efficient suicide prevention by the World Health Organization (WHO) [10]. These observations underscore the need to develop tools to help self-recognition of suicidal risk and associated mental disorders in the general population, as well as to encourage help-seeking behaviors in this population. Given the high, and constantly increasing, rate of Internet access [11] and smartphone ownership [12], e-health programs could usefully complement current suicide-prevention measures in addressing the remaining challenges. It is estimated that an increasing share of the population resorts to the Internet in search of answers to their health concerns [13, 14], and this is particularly the case for mental health [15, 16]. It has also been shown that health-information-seeking on the Internet is higher among those with stigmatized health conditions, including depression and anxiety, and that users with these conditions increase their utilization of healthcare after accessing such information [17, 18].

The StopBlues program, including a smartphone application and an associated website, was developed in this context. This program is available free-of-charge for the general population living in France. Its content, accessible only to users aged over 18 years (as declared at the first connection), is evidence-based and was built based on previous literature reviews [19, 20] and on advice from expert groups, including people who have experienced psychological distress (participatory design process). All in all, the StopBlues program provides a comprehensive prevention approach including awareness strategies (provision of general information on mental health, stigma, benefits of help-seeking, etc.), screening strategies (mood-tracking and self-assessment questionnaires), strategies for accessing support (locator of nearby helps and emergency “get help now” button) and mental health strategies (safety plan and toolbox with relaxation and mindfulness exercises) as recommended by previous research [19].

However, e-health programs for suicide prevention should be associated with effective promotion strategies to ensure that people who could benefit from these programs are aware of them, as well as to help them identify reliable programs among those available online and encourage their use [19, 21]. In parallel with this targeted effect, such promotion campaigns may have ecological effects similar to those previously observed for other awareness campaigns [22–24], by decreasing the stigmatization associated with mental health issues in civil society, and changing the attitudes and norms associated with psychological distress in the adult general population. This would in turn facilitate help-seeking behaviors, leading to a decrease in the occurrence of psychological distress and suicidal ideations, and ultimately preventing suicidal acts. Suicide-prevention measures deployed in the community have been shown to be particularly effective in several studies [25–28], and previous research has involved cities or counties in the development of such measures [29, 30]. The additional involvement of health professionals, in particular general practitioners (GPs), in promotion campaigns for suicide prevention carried out at the local level could also be beneficial. Indeed, even if people with mental disorders prefer not to seek formal professional help [22], GPs are the health specialists whom people suffering from psychological distress or at risk of suicide most easily turn to, even if not always addressing these topics directly. Among people who committed suicide, 20% did so within 1 day of a visit to their GP [31]. Involving local authorities as well as GPs in promoting suicide-prevention actions through dedicated interventions could, therefore, have complementary benefits, provided that they address the potential lack of sufficient skills, as well as of technical, financial and human resources at their level. However, to the best of our knowledge, no study has involved a large number of local actors in the promotion of an evidence-based e-health tool for suicide prevention, although the development of promotion measures for e-health programs has been advocated by previous work [19, 21].

### Objectives of the trial

#### Primary objective

In this context, the primary objective of our trial (“*Programme de Recherche INTerventionnelle et Evaluative Mené pour la Prévention du Suicide*”, PRINTEMPS) is to assess the effectiveness of an intervention which includes a tailored, local-level promotion of the StopBlues program, and to compare the effectiveness of two types of local promotion (with or without a passive involvement of GPs through their waiting rooms) on deaths by suicide and suicide attempts over a 12-month period.

#### Secondary objectives

The secondary objectives will be measured both at the cluster level (geographical area sharing a common authority) and among users of the StopBlues program.

Secondary objectives considered at the cluster level are as follows:
To assess the cost-effectiveness and to run a budgetary impact analysis of the intervention

Secondary objectives measured among users of the StopBlues program are as follows:
2.To assess the effectiveness of the intervention in terms of the intensity of the utilization of the program3.To assess the effectiveness of the intervention for help-seeking behaviors and participation in supportive activities (any activity that a user finds beneficial for their mental health)4.To assess the effectiveness of the intervention for the evolution of the level of psychological impairment

It should be noted that an additional form of promotion (more sustained promotion by local authorities, described below) will be implemented after 12 months in the control group and evaluated using the same primary outcome measure. In parallel, the long-term effectiveness of the two main types of local promotion (with or without a passive involvement of GPs through their waiting room) will also be assessed.

## Methods/design

### Study design

This study will be implemented as a three-arm, parallel-group, cluster-randomized controlled superiority trial, with before-and-after observation. Cluster-randomization was deemed mandatory because of potential contamination issues. Indeed, the very nature of the intervention assessed (i.e., a promotion program) cannot be applied at the individual level. This is typically a cluster-cluster intervention, as defined by Eldridge et al. [32]. Clusters were defined as geographical areas sharing a common local authority. These local authorities can either be cities or a grouping of cities (“*communautés de communes*” or “*communautés d’agglomérations*”) based on the local health governance of each area. If several adjacent local authorities volunteer individually to participate in the trial, they will be considered as a unique local authority.

Clusters will be randomly assigned to one of the following three arms with a ratio of 1:1:1:
Arm 1: no promotion of the StopBlues program (*control group*)Arm 2: promotion of the StopBlues program by local authorities only (*basic promotion group*)Arm 3: promotion of the StopBlues program by local authorities with an additional passive involvement of GPs through their waiting rooms (*intensified promotion group*)

The initial trial duration will be of 12 months. Baseline data on the number of suicidal acts, collected 12 months prior to the intervention, will also be considered in each cluster. After a 12-month post-randomization period, clusters from the control group will be allowed for a further 12-month period to launch their promotional campaign supported by the research team through regular contacts and additional technical and financial resources in comparison to arms 2 and 3 (*more sustained promotion by local authorities*). This will facilitate the recruitment of clusters as well as their adherence to the intervention during the first 12-month period [33]. It will also enable us to determine whether promotion led by local authorities could be improved by supporting them in the provision of additional promotional resources.

A complete description of the different steps of the trial is presented in Fig. 1 using the Timeline cluster tool of Caille et al. [34].

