### Intervention to be evaluated

The intervention evaluated corresponds to the tailored local promotion of the StopBlues program. Its description below complies with the Template for Intervention Description and Replication (TIDieR) Checklist for intervention description [38].

The StopBlues program will be promoted by the French local authorities participating in the trial. A basic communication toolkit, including a promotion guide, posters, leaflets and key communications messages, will be provided to each local authority at the beginning of the intervention. In addition, a contact person from the municipal staff already involved in health prevention will be appointed in each local authority. They will be in charge of coordinating the promotion of the StopBlues program at the local level and will participate in a day-long training session prior to the beginning of the promotion campaign. Local authorities will then be in charge of promoting the program by choosing their usual municipal communication medium (local newspapers, bulletins and billboards, posters in local shops and bus stops, etc.), by involving local actors of their choice and by developing additional promotion tools if they wish. They will, therefore, be able to develop a tailored intervention adapted to their local context.

Additional promotion of the StopBlues program (intensified promotion) will be carried out in several local authorities by the additional involvement of local GPs. As GPs’ workload is significant in France, due to the fact that they have been put at the heart of care coordination [39], a passive involvement of GPs in the promotion of the StopBlues program was designed. They will receive communication tools on the StopBlues program, such as leaflets or posters, to put in their waiting rooms in order to inform patients and their relatives about the existence of the program.

Finally, the local authorities of the control group will be offered a more sustained promotion at 12 months, which is not part of the main intervention but will also be evaluated during the trial. This promotion will consist of the same promotion as in the basic promotion group to which will be added regular support from the research team with stronger contacts and technical and financial resources for local authorities to implement the promotion and print the tools (flyers, posters, etc.). The inclusion of GPs in this promotion process will be left to local authorities’ discretion.

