#### Effectiveness of the more sustained promotion by local authorities

The effectiveness of the more sustained promotion by local authorities will be measured by the numbers of deaths by suicide and suicide attempts considered separately in the 12 months following the start of this form of promotion in the control group.

Table 2 provides a summary of all outcome measures collected by level of availability as well as their timeframe.

If users of the StopBlues program stop connecting to it, they will receive push-up notifications on their smartphones or reminder emails regarding the completion of questionnaires, to improve adherence.

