#### Statistical considerations

Characteristics of local authorities and of users of the StopBlues program will be described by the mean and standard deviation (SD) for continuous variables or by number (%) for categorical variables.

To assess the effectiveness of the intervention on the primary outcome (number of suicidal acts at the local authority level), we will compare the number of overall suicidal acts at 12 months and of suicides and suicide attempts separately between the trial arms adjusted on the number observed during the 12 months before the intervention.

We will use a Poisson regression analysis with clusters as analysis units and cluster size as offsets and adjust for baseline data and local authorities’ characteristics (population size, ecological index of deprivation, type of local authorities forming the cluster, etc.). A similar method will be used for all secondary outcomes measured at the level of local authorities.

For secondary outcomes measured on the users of the StopBlues program, mixed-model repeated-measures analyses will be used. This method will enable the inclusion of all users regardless of their level of adherence to the program, which will allow us to carry out the analysis despite some missing values. Adjustments will be made on the initial level of psychological distress of each user and on demographics. By using mixed-model repeated-measures analyses [61], we will also be able to account for potential clustering effects through the incorporation of adequate random effects for local authorities. Transformation of outcome variables will be done as necessary to meet distributional assumptions and to accommodate potential outlying observations. Additional subgroup analyses will be carried out to assess separately the effect of the intervention on users with a history of suicide attempts and those without.

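### Year 2 compares whole promotion strategies; it cannot isolate the value of extra support, as the Study design section says it will

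*Protocol article*

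**What the plan says.** After the first 12 months, "clusters from the control group will be allowed for a further 12-month period to launch their promotional campaign supported by the research team" (Study design). The extra help is described as "additional technical and financial resources in comparison to arms 2 and 3". The same section then gives the purpose: "It will also enable us to determine whether promotion led by local authorities could be improved by supporting them".

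The section Intervention to be evaluated defines the package: "This promotion will consist of the same promotion as in the basic promotion group to which will be added regular support from the research team". It adds: "The inclusion of GPs in this promotion process will be left to local authorities" to decide. Table 1 defines the basic arm as local promotion that does not involve GPs; GP waiting rooms are what separates arm 3 from arm 2.

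The section on the effectiveness of the more sustained promotion counts deaths and attempts "in the 12 months following the start of this form of promotion in the control group" and names no comparator. Statistical considerations gives a Poisson model for the primary outcome, compared between arms and adjusted for the pre-trial 12 months, and then says: "A similar method will be used for all secondary outcomes measured at the level of local authorities".

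**The concern.** The Study design sentence promises to determine whether support improves authority-led promotion. That is a claim about one ingredient, the support. To read a difference as the effect of that ingredient, the arms compared should otherwise be alike. Here they also differ in how long promotion has been running, and possibly in GP involvement, which each former control authority chooses after randomisation.

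At stake is what may be concluded from the second year. A favourable result could be reported as evidence that support works when it reflects a fresh campaign set against an ageing one, or GP waiting rooms. An unfavourable result could be reported as evidence that support is useless when basic promotion has simply had longer to build. According to Ethical considerations, funders and health authorities take part in the decision on continuation after the trial, so the wording of this conclusion matters.

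**Working it through.** **The plan's own figures.** The protocol gives no figure for the year-2 question. Its year-1 planning figures are sound and serve only as inputs here. The reduction is (0.215 - 0.190)/0.215 = 11.6%. The stated total of 1,229,350 is reproduced as 2 x 614,678 = 1,229,356 (two proportions, pooled variance, two-sided 2.5%, 80% power).

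**Available comparisons for sustained promotion (former control, months 13-24).**

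- Against arm 2 in months 13-24: randomised and in the same calendar period. It sets first year since launch against second, and optional GP use against none.
- Against arm 2 in months 1-12: same year since launch, but a different calendar year, and GP use still differs.
- Against its own months 1-12: before-after in calendar time, and it contrasts sustained promotion with no promotion, not with basic promotion.

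None isolates support. The first is the only one that is both concurrent and randomised.

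**What the concurrent contrast estimates.** Let B1 and B2 be the rate multipliers of basic promotion in its first and second year, S1 the first-year multiplier of basic promotion plus support, and G the extra multiplier from GP use in the former control arm. Then

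rate ratio = (S1 x G)/B2 = (S1/B1) x (B1/B2) x G.

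Only S1/B1 is the effect of support. The contrast equals it when B1 = B2 and G = 1. B1 can be estimated from arm 2 against control in year 1. B2 cannot be estimated without further assumptions, because in the design as described no arm is left without a promotion campaign in months 13-24.

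**Illustrations (assumed values; support adds nothing, so S1/B1 = 1).**

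- Basic effect halves, from 11.6% to 5.8%, with G = 1: (1 - 0.116)/(1 - 0.058) = 0.884/0.942 = 0.94.
- Basic effect builds, from 5.8% to 11.6%, with G = 1: 0.942/0.884 = 1.07.
- Basic effect stable, GP use lowering the arm's rate by 3%: ratio 0.97.

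**How often such a difference would look significant.** Inputs from Sample size and power: 11 clusters of 138,172 per arm, ICC 10^-5, rate 0.190% under basic promotion. Assumed: two-sided 5% test.

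- Inhabitants per arm: 11 x 138,172 = 1,519,892.
- Design effect: 1 + 138,171 x 0.00001 = 2.38. Effective size per arm: about 638,000.
- For a 5% difference, the rates are 0.190% and 0.1805%, a gap of 0.0095 percentage points. The standard error is about 0.0076 points, so z is about 1.25 and the chance of significance about 24%.
- For 2% and 10% differences the chances are about 7% and 72%.

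These use combined suicidal acts, whereas the sustained-promotion outcome treats deaths and attempts separately. They show scale only.

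**The case against.** This is an ancillary aim. The protocol says that sustained promotion is not part of the main intervention. The Secondary objectives section mentions it only after the numbered list, and the first reason given for it is recruitment and adherence of control clusters. That stands, and it limits the weight of the point.

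The months 13-24 contrast is randomised and gives relevant evidence on whether a supported campaign does better than an unsupported one already under way. That also stands. A reader might infer that year 2 can say nothing about sustained promotion; the documents do not support that.

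A reader might also infer that the trial will judge sustained promotion before-after or against arm 2's first year. No section proposes either. Statistical considerations compares arms and extends a similar method to cluster-level secondary outcomes, which points towards a between-arm contrast. A condensed article may leave the exact comparator to a fuller document.

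On GPs, arm 2 authorities may also involve local actors of their choosing, users report whether they heard of the program in a GP waiting room, arm 3 against arm 2 gives a randomised estimate of the GP component, and a process evaluation is planned. These help to describe and bound the GP contribution. They do not remove the mixing: Table 1 keeps GPs out of arm 2, and adjusting for a choice made by authorities after randomisation does not restore a randomised comparison.

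Finally, the rate ratios rest on assumed time courses that have no source in the protocol. That is correct, and they carry no weight beyond illustration.

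**Conclusion.** The point holds as an overstated claim. The design permits a valid randomised comparison of two whole strategies in months 13-24: the first year of basic promotion plus support with optional GP involvement, against the second year of basic promotion. It does not isolate support, and an analysis model cannot repair this without assuming how the basic effect changes over time and how much GP use contributes.

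The size of the distortion is unknown. On the assumed fade and build patterns, a support effect of zero would appear as 0.94 or 1.07, so even the direction is not fixed. This takes arms 2 and 3 to be in a second promotion year; if their campaigns lapse, the contrast becomes active against lapsed promotion and is further from isolating support.

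It would go too far to conclude that optional GP involvement must be barred. The documents do not require it, and the first-year versus second-year difference would remain. The matter concerns a secondary evaluation only.

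**What to change.** 1. In Study design and in the section on the effectiveness of the more sustained promotion, name former control versus arm 2 in months 13-24, adjusted for the pre-trial 12 months, as the comparison on which inference about sustained promotion rests.
2. Replace the claim to determine the effect of support with a statement that the trial will compare the first year of the sustained package (support plus optional GP involvement) with the second year of basic promotion.
3. State that this reflects added support only if the basic effect is stable from year 1 to year 2 and GP use contributes nothing.
4. Record GP involvement for each cluster and report it descriptively.

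The cost is wording in two sections and one item recorded per cluster. The downside is a narrower claim for this secondary evaluation. What control authorities are offered and the primary 12-month comparison do not change.
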